### Data Collection

Data were collected with research data management software, including REDCap (Research Electronic Data Capture), a web-based application designed specifically for clinical research for consent tracking and data validation. A detailed schedule of data collection and a CONSORT (Consolidated Standards of Reporting Trials) flowchart of the study protocol, including baseline data collection, intervention, and follow-up, is shown in Figure 3.

**Figure 3 figure3:**
[figure not shown]
CONSORT (Consolidated Standards of Reporting Trials) flowchart of Healthy Smiles. ICDAS: International Caries Detection and Assessment System; KI: potassium iodide; SDF: silver diamine fluoride.

### Phase 1: Baseline Data Collection

#### Sociodemographic Details

The details about the Healthy Smiles will be clearly explained at a parent-teacher association meeting. Parents who give consent for participation will be considered. A standard form will be designed on Google Forms to collect sociodemographic details, comprising basic information such as name, age, sex, school grade, school, and address. Data will be protected and kept confidential.

#### Clinical Examinations

Clinical examinations will be performed by visual inspection under visible light, with the children in an upright position. The children will be assessed for dental caries using ICDAS codes and criteria. ICDAS codes 0-3 can be determined with air drying. Using a ball-ended World Health Organization (WHO) Community Periodontal Index probe, cavitated lesions (ICDAS codes 5 and 6) will be probed.

### Phase 2: Intervention

The Healthy Smiles study sample will comprise 2 groups: group 1 will receive 38% SDF (Riva Star; SDI Inc); group 2 will receive 38% SDF with 10% KI (Riva Star; SDI Inc).

#### Method of Application

In group 1, we will use cotton gauze to carefully clean and dry the affected tooth surface. The gingival tissue of the tooth will be protected with petroleum jelly. An applicator will be dipped into the SDF and 2-3 mg will be applied to the lesion with a microbrush, which will be used to paint the solution over the carious lesion; then, we will wait for 1 minute for absorption.

In group 2, we will apply SDF with the same technique. After the SDF application, KI will be applied using a separate microbrush, which will be saturated with the solution and will be used to paint the solution over the carious lesion. No rinse will be performed and special instructions will be given following application.

After treatment, an individual report on the child’s oral health will be provided, and after-treatment instructions will be given to the parents. If there is any adverse drug reaction associated with the SDF treatment, the parents will be asked to contact the principal investigator immediately by telephone.

All teeth will be photographed immediately after treatment. A high resolution mobile camera will be used to capture all of the images throughout the study. The high-resolution mobile camera features a 64-megapixel primary camera with an 8-megapixel secondary depth camera and an 8× optical zoom to provide images at a 2340×1080-pixel resolution.

Each tooth’s color will be measured using a Nix Mini color sensor. The Nix Mini color sensor is a wireless colorimeter that uses artificial intelligence to measure the exact color of surfaces and transmits the digital color values to a smartphone or tablet using Bluetooth.

Measurements will be calibrated in accordance with the manufacturer’s instructions to determine the first shade of the carious lesion. The ∆L and ∆E values will be measured 3 times by a single operator, and the average values will be noted. Despite the fact that SDF treatment had no adverse effects in other studies, if any adverse events occur, the primary investigator will duly report them to the institutional ethics committee.

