### Phase 3: Follow-Up

#### Primary Outcome Measures

Staining propensity will be measured 1, 3, and 6 months after treatment. Evaluation of the change in color of the carious lesions will use photographs and the Nix Mini color sensor.

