#### Secondary Outcome Measures

The arrest of carious lesions will be measured 6 and 12 months after treatment. The size of the carious lesions will be evaluated using the ICDAS index as stable or progressing. The consistency of the lesions will be evaluated with gentle probing using a ball-ended WHO probe as soft or hard. The level of satisfaction will be measured immediately after intervention. Parental satisfaction with dental appearance and color following treatment with SDF and SDF+KI will be assessed using a prevalidated 4 item, 5-point Likert-scale questionnaire in English developed by Clemens et al [20] in 2018.

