### Risks and Discomforts

There are no major known risks to the study. There are minor risks, such as black stains on the carious tooth surface or temporary stains on the skin. Temporary stains on the skin will disappear within 48 hours without treatment. Participants who are allergic to the products will be excluded from the study.

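### After the treatment day, the only stated route for adverse events is a parent's call about a reaction tied to SDF; it depends on parental attribution and does not name KI

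*Protocol article*

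**What the plan says.** All places are in the protocol article.

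- **Collection (Method of Application).** "If there is any adverse drug reaction associated with the SDF treatment, the parents will be asked to contact the principal investigator", at once and by phone.
- **Onward reporting (end of the same section).** "Despite the fact that SDF treatment had no adverse effects in other studies", the sentence begins, and it continues: "if any adverse events occur, the primary investigator will duly report them to the institutional ethics committee".
- **Difference between the arms (same section).** "In group 2, we will apply SDF with the same technique. After the SDF application, KI will be applied using a separate microbrush". Both groups receive 38% SDF.
- **Timing.** Under Primary Outcome Measures, "Staining propensity will be measured 1, 3, and 6 months after treatment". Under Secondary Outcome Measures, caries arrest is assessed at 6 and 12 months, and for the parental questionnaire "The level of satisfaction will be measured immediately after intervention". Two of its four items in Table 1 ask about pain and taste, and both name SDF and SDF+KI.
- **Known effects.** Ethical Considerations says that parents will be informed of adverse effects and singles out tooth discoloration. Risks and Discomforts lists black staining of the carious surface and temporary skin stains: "Temporary stains on the skin will disappear within 48 hours without treatment".
- **Analysis.** Safety is not among the objectives, the primary or secondary outcomes, or the comparisons under Data Analysis.

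**The concern.** What the investigator can report is limited by what the investigator hears. The collection instruction asks a parent to decide that something is a drug reaction, link it to SDF and make a call. Each step loses events. The instruction names the agent that both arms share and leaves out the one that differs, so it is at best ambiguous about the experimental component.

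At stake is the meaning of a later statement that no adverse events occurred. Under this rule, such a statement could reflect few events or few calls, and a reader could not tell which. There is also a definitional problem. The article says that SDF had no adverse effects in other studies, yet elsewhere treats discoloration as an adverse effect. It does not say whether blackening of the lesion, which is what the primary outcome measures, falls under the duty to report any adverse event.

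**Working it through.** **1. Scope of the two sentences in Method of Application.** The collection sentence covers reactions associated with the SDF treatment, as judged by a parent. The reporting sentence covers any adverse event, with no limit by agent or arm. The second governs events already known, so it cannot widen the first. For events at home after the treatment day, the narrower sentence decides what is recorded.

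**2. Timeline.** On the treatment day, parents answer four items, of which pain and taste bear on tolerability. Both rate the application itself. The next scheduled assessment is at 1 month. The one duration that the article gives for a transient effect is 48 hours (skin stain). An effect of that length arising at home is over before the first follow-up visit and is recorded only if a parent calls.

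**3. Consistency of the safety statements.** Method of Application says that other studies of SDF showed no adverse effects. Ethical Considerations names tooth discoloration as an adverse effect, and Risks and Discomforts lists black stains and skin stains. As worded, these do not agree.

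**4. Illustration of size.** The article states no adverse event rate, reporting rate or safety power, so there is no figure to reproduce. The only input from the article is n = 30 per arm (Statistical Power). The true rate r and the share reported c are assumptions.

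P(no report in an arm) = (1 − r × c)^30

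| True rate r (assumed) | c = 100% | c = 50% | c = 25% |
|---|---|---|---|
| 5% | 0.95^30 = 0.21 | 0.975^30 = 0.47 | 0.9875^30 = 0.69 |
| 10% | 0.90^30 = 0.04 | 0.95^30 = 0.21 | 0.975^30 = 0.47 |
| 20% | 0.80^30 = 0.001 | 0.90^30 = 0.04 | 0.95^30 = 0.21 |

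With full capture, 0 of 30 gives a one-sided 95% upper bound of 1 − 0.05^(1/30) = 9.5%. With incomplete capture, this bounds only the product r × c. It cannot be turned into a bound on r without knowing c, which the article does not give.

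**5. What better capture would not achieve.** Take true rates of 5% and 20% (assumed), 30 per arm and a two-sided 5% test. Power = Φ[(|p2 − p1| − 1.96 × SE0) / SE1], where SE0 is the pooled and SE1 the unpooled standard error. With full capture, SE0 = √(2 × 0.125 × 0.875 / 30) = 0.0854 and SE1 = √((0.05 × 0.95 + 0.20 × 0.80) / 30) = 0.0832. Power is therefore Φ[(0.15 − 0.1674) / 0.0832] = Φ(−0.21) = 0.42. Multiplying both rates by c gives 0.22 at c = 50% and 0.13 at c = 25%. The trial is too small for a firm safety comparison even with complete reporting.

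**The case against.** The strongest reply has five parts.

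- **No safety comparison is planned.** This stands. A reader might infer that a KI safety comparison will look falsely clean. The documents do not support that, because no such comparison is among the objectives, outcomes or analyses. The conclusions speak of not compromising effectiveness, which is a different claim from absence of harm.
- **KI is not clearly excluded.** This stands in part. The SDF treatment can be read to include the SDF+KI regimen, and a parent in group 2 could hardly separate the two agents. A reader might infer that events in the SDF+KI arm are under-counted by rule, but passive reporting lowers counts in both arms. A KI-specific deficit would need differential under-reporting, which the wording makes possible but does not show. The ambiguity remains, because Table 1 and the Randomization section write SDF and SDF+KI as separate terms.
- **Some tolerability data are solicited.** This stands. Pain and taste are asked in both arms on the treatment day with KI named, so the point is confined to the period after that day.
- **An article condenses the full protocol.** This stands for forms, checklists and soft-tissue checks, whose absence is not criticised here. The after-treatment instructions are not reproduced, and the schedule figure is not shown in the text at hand. It does not answer the point about the collection rule, which the article does state.
- **Nothing says that blackening will be filed as an adverse event.** True. The text leaves it unsettled, and one sentence would settle it.

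**Conclusion.** The point holds in a limited form. After the treatment day, the stated collection rule is passive, depends on parental attribution, does not name KI, and is narrower than the reporting duty in the same section. A report of no adverse events would therefore be weakly informative in either arm. The size cannot be fixed from the article. On assumed true rates of 5% to 20%, the chance of no report in an arm of 30 is 0.001 to 0.21 with full reporting, 0.04 to 0.47 if half are reported, and 0.21 to 0.69 if a quarter are. The conflict between the no-adverse-effects statement and the two later sections needs no assumption. No stated objective, estimate or planned test is affected. This is a modest but worthwhile improvement in safety ascertainment, and it assumes that the unseen full protocol does not already state a wider rule.

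**What to change.** 1. Reword the parent instruction in Method of Application to cover any adverse event after application of SDF or KI, whether or not it is thought to be related. Its scope then matches the reporting sentence in the same section.
2. Ask the same brief adverse event questions in both arms at the visits already scheduled, covering the whole interval since treatment. One early call per child, 60 in all, is optional and would reduce reliance on recall for short-lived effects.
3. Reconcile the statement that SDF had no adverse effects in other studies with Ethical Considerations and Risks and Discomforts. State that blackening of the treated lesion is recorded as the outcome.

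The cost is a wording change and a short form, with no extra visits. More minor events will be reported. Even with these changes, 30 children per arm will not support a firm comparison of safety, so events should be described by arm.

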### Phase 3: Follow-Up

#### Primary Outcome Measures

Staining propensity will be measured 1, 3, and 6 months after treatment. Evaluation of the change in color of the carious lesions will use photographs and the Nix Mini color sensor.

#### Secondary Outcome Measures

The arrest of carious lesions will be measured 6 and 12 months after treatment. The size of the carious lesions will be evaluated using the ICDAS index as stable or progressing. The consistency of the lesions will be evaluated with gentle probing using a ball-ended WHO probe as soft or hard. The level of satisfaction will be measured immediately after intervention. Parental satisfaction with dental appearance and color following treatment with SDF and SDF+KI will be assessed using a prevalidated 4 item, 5-point Likert-scale questionnaire in English developed by Clemens et al [20] in 2018.

### Data Analysis

Data will be analyzed using SPSS (version 28; IBM Corp). Descriptive statistics will include the mean and SD for continuous data and frequency and percentage for categorical data. An independent-sample 1-tailed *t* test or the Mann-Whitney *U* test will be used for comparing the 2 groups. *P* values will be considered statistically significant at ≤.05.

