In order to overcome this problem and increase the clinical use of SDF, a new method of application has been suggested [15]. This includes treating the initial layer of SDF with a layer of potassium iodide (KI), which combines with the free silver ions in SDF and inhibits the precipitation of silver phosphate. Since then, numerous investigations have shown that using KI after SDF creates a yellow silver iodide precipitate and prevents tooth stains from turning dark [10,16]. Following the application of KI in a dose-dependent manner, Detsomboonrat et al [17] noticed a considerable and immediate reduction in staining caused by SDF.

Studies demonstrating that KI reduces black staining are still insufficient. This paper presents the study protocol for Healthy Smiles, a randomized controlled trial implemented to compare the staining propensity of SDF+KI.

The aim of the study is to evaluate the staining propensity of SDF+KI among children aged 4 to 6 years by incorporating artificial intelligence in dentistry as a tool for precise interpretation of the findings, which will add to the evidence pool. The objectives of the study include (1) to evaluate the staining propensity of SDF+KI using a Nix Mini color sensor (Nix Sensor Ltd) among children aged 4 to 6 years, (2) to evaluate the caries-arresting effect of SDF+KI in the treatment of carious primary teeth, and (3) to assess parental satisfaction with dental appearance and color following treatment with SDF versus SDF+KI using a detailed questionnaire (Table 1). We hypothesized that there would be no difference in the staining propensity of SDF+KI among the children.

**Table 1 table1:** Objectives and measures.

Objectives	Measures	Description
1. To evaluate the staining propensity of SDF^a^ and SDF plus KI^b^ using the Nix Mini color sensor among children aged 4 to 6 years.	Child dental examination	At the end of 1, 3, and 6 months after treatment each tooth will be photographed and each tooth’s color change will be measured using the Nix Mini color sensor.
2. To evaluate the caries-arresting effect of SDF and SDF+KI in the treatment of carious primary teeth.	Arrest of carious lesions (6 and 12 months after treatment)	The progression in the size of the carious lesions will be evaluated using the ICDAS^c^ index as stable or progressing. The consistency of the lesions will be evaluated upon gentle probing using a ball-ended World Health Organization probe as soft or hard carious lesions.

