**Inclusion criteria**
Children aged from 4 to 6 yearsChildren who meet the criteria for International Caries Detection and Assessment System (ICDAS) code 1 or greaterChildren who have one or more active carious lesions in primary teeth not involving the pulpParents who give consent for participation in the study

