### Randomization

The names of 60 children will be selected randomly with a computer-generated table of random numbers by an independent assistant using the Stat Trek (StatTrek.com) random number generator. The names will be randomly distributed into 2 groups (SDF and SDF+KI) with a lottery method for the next phase. For the trial, 2 groups will be assigned: group 1 and group 2. The assistant, who is independent of the trial, will be responsible for giving each child a serial number indicating his or her allocation. Blinding of the examiner or the children will be impossible during the intervention and follow-up due to the different natures of the materials. However, the assistant, who will be responsible for giving and collecting the questionnaires from the parents or guardians, as well as the statistician, will not know the group to which the child belonged.

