### Statistical Power

The sample size was calculated with G*Power (version 3; Universität Düsseldorf). Based on the results of Aly and Yousry [18], at a 5% level of significance and 95% power with an effect size of 1.594, (calculated by considering that the mean lightness value of one group was 71.3, SD 14.2 and the other group was 53.6, SD 6.7), and the primary end point being an evaluation of the staining propensity of SDF+KI at the end of 1, 3, and 6 months after treatment, with a 95% chance of detecting an increase in the mean lightness value from 53.6 in the control group to 71.3 in the experimental group, the minimum sample size in each group is 16. The expected dropout rate is 10%, so after considering the dropout rate, the sample size in each group is 30. Thus, the total sample required for the intervention will be 60 children (N=60).

For the secondary objective, with a significance level of 5%, a power of 80%, and an estimated critical *Z* value of 3.193, the study required 48 teeth, or 24 teeth per group. Finally, assuming 40% loss to follow-up, a sample size of 34 teeth was gathered in each group [19] to evaluate the caries-arresting effect of SDF+KI in the treatment of carious primary teeth at 6 and 12 months after treatment.

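### Caries arrest is counted in teeth although children are randomised, and the independent-sample tests named make no allowance for several teeth from one child

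*Protocol article*

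**What the plan says.** **Allocation.** The Randomization section allocates children: "The names will be randomly distributed into 2 groups (SDF and SDF+KI) with a lottery method". Statistical Power sets 30 children per group.

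**Lesions per child.** The inclusion criteria in Textbox 1 admit children who "have one or more active carious lesions in primary teeth". The article states no index tooth, upper limit or child-level summary.

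**Colour (primary).** Table 1 says of each tooth that its "color change will be measured using the Nix Mini color sensor", and Method of Application likewise takes a reading per tooth. The sample size for this outcome is nevertheless given in children.

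**Caries arrest (secondary).** Lesion size is recorded in two categories: "The size of the carious lesions will be evaluated using the ICDAS index as stable or progressing". Consistency is recorded as soft or hard. The sample size is in teeth: "the study required 48 teeth, or 24 teeth per group", and then, "assuming 40% loss to follow-up, a sample size of 34 teeth was gathered in each group". Statistical Power mentions no ICC and no design effect.

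**Analysis.** The only between-group comparison in Data Analysis is this: "An independent-sample 1-tailed *t* test or the Mann-Whitney *U* test will be used for comparing the 2 groups". The Abstract names the same two tests. Categorical data are to be summarised by counts and percentages.

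**The concern.** Both named tests need independent observations. Teeth in one mouth share diet, saliva, hygiene and the same treatment visit, so their outcomes are likely to be positively correlated. Because a whole child is allocated to one arm, that correlation adds to the variance of the difference between arms. A test that counts each tooth as a separate participant leaves the added variance out. Its standard errors and p values are then too small and its confidence intervals too narrow.

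For arrest this follows from what the plan states. For colour it depends on a choice that the article does not make: one value per child would be valid, one value per tooth would not. Leaving that open also allows the choice to be made after the data are seen. Arrest matters beyond its secondary rank, because the Conclusions present the trial as a way to improve appearance without loss of SDF effectiveness.

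**Working it through.** **Inputs from the article.** Children per group: 30. Teeth per group for arrest: 24, raised to 34. Nominal level: 5%, with a 1-tailed t test.

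**Inputs assumed, because the article does not give them.** ICC between teeth of one child: 0.2 to 0.5. Teeth per child: 34/30 as the plan implies, and 2 to 3 in case every eligible tooth is used.

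**Step 1. The plan's own figure.** The 24 teeth per group cannot be recomputed, since no arrest rates are given. The inputs are stated as "with a significance level of 5%, a power of 80%, and an estimated critical *Z* value of 3.193", whereas 5% and 80% give 1.96 + 0.84 = 2.80 (two-sided) or 1.645 + 0.84 = 2.49 (one-sided). The 34 is reproduced as 24 × 1.4 = 33.6, rounded up. (Dividing by 1 − 0.40 would give 40. This and the Z value are separate matters.) Loss alone thus accounts for the step from 24 to 34, with no factor for clustering in it.

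**Step 2. Must any child give more than one tooth?** 34/30 = 1.13 teeth per child, so yes. The most even split is 26 children with one tooth and 4 with two: 26 + 8 = 34.

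**Step 3. Design effect (DE).** For m teeth per child, DE = 1 + (m − 1) × ICC. For unequal numbers, replace m by Σm²/Σm. With 26 ones and 4 twos this is (26 + 16)/34 = 1.235.

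**Step 4. True one-sided error of a nominal 5% test** = P(Z > 1.645/√DE).

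| Teeth per child | ICC | DE | One-sided error |
|---|---|---|---|
| 34/30, simple mean 1.13 | 0.2 | 1.03 | 5.2% |
| 34/30, simple mean 1.13 | 0.5 | 1.07 | 5.6% |
| 34/30 as 26 ones, 4 twos | 0.2 | 1.05 | 5.4% |
| 34/30 as 26 ones, 4 twos | 0.5 | 1.12 | 6.0% |
| 2 (assumed) | 0.2 | 1.2 | 6.7% |
| 2 (assumed) | 0.5 | 1.5 | 9.0% |
| 3 (assumed) | 0.2 | 1.4 | 8.2% |
| 3 (assumed) | 0.5 | 2.0 | 12.2% |

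Example, last row: 1.645/√2.0 = 1.163, and the area beyond it is 12.2%.

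**Step 5. Does clustering leave arrest short of information?** With 30 children and 2 teeth each there are 60 teeth per group, worth 60/1.5 = 40 independent teeth at ICC 0.5. With 3 each, 90/2.0 = 45. After the plan's 40% loss, 18 children remain: 36/1.5 = 24 and 54/2.0 = 27. Neither is below the 24 required.

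**Step 6. Does the lack of a test for binary data matter?** Take, for illustration, 27/34 against 20/34 arrested. Mann-Whitney gives p = 0.068 and the uncorrected chi-square p = 0.066. The p value hardly moves.

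**The case against.** The strongest reply is that the article never states the unit of analysis. For colour the sample size is in children, and one value per child (a mean or a chosen tooth) fits both that count and an independent-sample test. That stands. A reader might infer that the colour p values will be too small, but the text does not show it; it shows only that the unit is not fixed.

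A second reply is that, on the plan's own count, the harm is slight. That also stands: at 34 teeth in 30 children the error is about 5% to 6%. The 34 is a target and not a cap, however, and nothing limits the teeth used per child, so a larger figure cannot be excluded.

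A third concerns information. A reader might argue that 24 teeth at a design effect of 1.5 to 2.0 are worth only 24/1.5 = 16 to 24/2.0 = 12. But 24 teeth at 2 to 3 per child come from 12 to 8 children, whereas 30 per group are enrolled. Step 5 shows that this reading fails.

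A fourth is that a condensed article may leave the pairing of tests with outcomes to an analysis plan that is not shown. That answers most of the complaint about binary data. It does not answer the clustering point for arrest, where the article itself sets a tooth count without a design effect beside tests that require independence.

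**Conclusion.** The point holds for caries arrest. As written, the plan would analyse teeth from the same child as independent, and its own figures make such teeth unavoidable. For colour it holds conditionally: the unit is undefined, and the error arises only if teeth are analysed.

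On the plan's own count the one-sided error is about 5.2% to 6.0% instead of 5%, with a design effect of about 1.03 to 1.12. This rests on an assumed ICC of 0.2 to 0.5 and the extra teeth spread as evenly as possible. If children give 2 to 3 teeth on average, the design effect is 1.2 to 2.0 and the error about 6.7% to 12.2%. That upper range should be read as what could happen without a rule, and not as what the documents show will happen.

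The missing test for binary outcomes is minor for the p value. Its practical consequence is that no difference in arrest proportions with an interval is promised. The clustering rule should be written down before analysis.

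**What to change.** **Data Analysis.** State that the child is the unit of inference for every outcome measured on teeth.

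- *Colour:* use a linear mixed model with a random effect for child (and for tooth within child if visits are modelled together), or take one mean per child at each visit. The second option keeps the tests already named.
- *Arrest (stable/progressing, soft/hard):* use generalised estimating equations clustered on child with a small-sample variance correction, or a proportion per child. At about 1.13 teeth per child a logistic model with a child random effect would be poorly identified, so these two are preferable. Report the difference in arrest proportions with a 95% confidence interval. Say in advance whether teeth or children carry equal weight, since the two options can differ on this.

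**Statistical Power.** Restate the power or precision of the tooth-based size with an assumed ICC, teeth per child and design effect. No additional children are called for.

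**Cost.** Analysis and wording only, with slightly wider confidence intervals. Choosing one index lesion per child before allocation would also have removed the problem, but enrolment began in October 2023, so it comes too late for children already allocated.

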**Methods:**

This study is a randomized controlled trial. A total of 60 children with caries that meet the criteria of the International Caries Detection and Assessment System (code 1 or above) will be randomly assigned to treatment groups, where group 1 will be treated with SDF and group 2 will be treated with SDF+KI. Discoloration of treated lesions will be assessed digitally using a Nix Mini color sensor. Participants will be followed up at 1, 3, and 6 months after treatment to digitally record the ∆L and ∆E values using the Nix Mini color sensor. Data will be analyzed using SPSS (version 28; IBM Corp). Independent sample *t* tests and the Mann-Whitney *U* test will be used to compare the 2 groups.

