### Conclusions

Healthy Smiles provides an opportunity to address the aesthetic inconvenience of patients without compromising the effectiveness of SDF treatment. This trial’s findings will contribute to the limited evidence base on discoloration after SDF intervention to improve aesthetic appearance in child oral health. If the results from the trial are promising, it will lead to the development of a model for child oral health and pave the way for further research in child oral health.

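### The t test is fixed as one-tailed at .05 without justification and the Mann-Whitney tail is left open; separately, the named difference tests cannot support wording about uncompromised effectiveness

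*Protocol article*

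**What the plan says.** **The tests.** Protocol article, Data Analysis: "An independent-sample 1-tailed *t* test or the Mann-Whitney *U* test will be used for comparing the 2 groups". The threshold is P ≤ .05. The tail is attached to the t test; none is given for the Mann-Whitney test. The Methods paragraph of the abstract names the same tests with no tail: "Independent sample *t* tests and the Mann-Whitney *U* test will be used to compare the 2 groups".

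**The hypothesis.** Introduction: "We hypothesized that there would be no difference in the staining propensity of SDF+KI among the children". It gives no direction and covers staining only.

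**The sample size.** Statistical Power sizes the primary outcome "at a 5% level of significance and 95% power with an effect size of 1.594", without saying whether the 5% is one- or two-sided. It does imply a direction for lightness: "detecting an increase in the mean lightness value from 53.6 in the control group to 71.3 in the experimental group". No direction is given there or elsewhere for ΔE, caries arrest or parental satisfaction.

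**Caries arrest.** Secondary Outcome Measures records lesions as stable or progressing and as soft or hard. Statistical Power asks for 24 teeth per group, raised to 34 for loss to follow-up. It gives no arrest rates and no margin. The Conclusions section, and the conclusions in the abstract, describe the project as a chance to deal with the aesthetic problem "without compromising the effectiveness of SDF treatment".

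**The concern.** A one-tailed test needs two things: a direction fixed in advance for each outcome, and a reason why a result the other way would be of no interest. The article supplies a direction for one outcome and a reason for none. Two consequences follow.

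- **Looser standard.** The evidence needed to declare a difference in the favoured direction is that of a two-sided test at .10. Where no direction is fixed (ΔE, arrest, satisfaction), the tail could be chosen after the data are seen. The same applies to the Mann-Whitney alternative, whose tail is not stated at all.
- **Blind side.** A test aimed at benefit from potassium iodide (KI) cannot flag a result in the opposite direction, however large.

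A separate problem lies next to this one. The wording about uncompromised effectiveness concerns the absence of a loss in caries arrest. A test for a difference does not address that, whatever its tail. If arrest does not differ significantly, the trial may simply have been too small to see a loss.

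**Working it through.** **1. The plan's own effect size.** The inputs are from Statistical Power: "mean lightness value of one group was 71.3, SD 14.2 and the other group was 53.6, SD 6.7".

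- Difference = 71.3 − 53.6 = 17.7
- Pooled SD = √[(14.2² + 6.7²)/2] = √[(201.64 + 44.89)/2] = 11.10
- d = 17.7/11.10 = 1.594, which reproduces the stated value.

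**2. The plan's minimum of 16 per group.** With the noncentral t distribution, d = 1.594, alpha 5% and power 95%, the t test needs 10 per group one-sided or 12 two-sided. The stated 16 does not reproduce either way, so it does not reveal which tail was assumed. It is more than enough for both.

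**3. What the single tail changes.** With 30 per group and the stated 10% dropout, 30 × 0.90 = 27 per group remain, so df = 2 × 27 − 2 = 52.

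| Test at .05 | Critical t, 52 df | False-positive rate in the favoured direction |
|---|---|---|
| One-tailed | 1.67 | 5% |
| Two-sided | 2.01 | 2.5% |

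**4. What a two-sided test costs on the primary outcome.** The noncentrality is d√(n/2), which is 1.594 × √8 = 4.51 at n = 16.

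| n per group | One-sided power | Two-sided power |
|---|---|---|
| 16 | 99.7% | 99.2% |
| 27 | >99.9% | >99.9% |
| 30 | >99.9% | >99.9% |

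**5. What a benefit-direction test misses.** This is an illustration on a continuous scale with 30 per group and assumed true effects in the unfavourable direction.

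| True effect | One-tailed test towards benefit rejects | Two-sided test flags harm |
|---|---|---|
| −0.5 SD | about 0.02% | 48% |
| −0.8 SD | about 0.0001% | 86% |

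**6. What the arrest comparison can show.** The article gives no arrest rates, so 70%, 80% and 90% in both groups are assumed. Teeth are treated as independent. The half-width of the 95% interval for the difference is 1.96 × √[2p(1 − p)/n].

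| Assumed arrest p | 24 teeth per group | 34 teeth per group |
|---|---|---|
| 70% | 25.9 points | 21.8 points |
| 80% | 22.6 points | 19.0 points |
| 90% | 17.0 points | 14.3 points |

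For example, at p = 80% and n = 24: 1.96 × √(0.32/24) = 1.96 × 0.1155 = 0.226. An observed difference of zero would then leave a loss of up to about 23 points within the interval.

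**The case against.** Several points on the other side are sound and limit what can be said.

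- **Scope of the tail.** A reader might infer that every comparison is one-tailed. The sentence does not say so: the tail belongs to the t test, and the Mann-Whitney tail is undefined.
- **Direction.** A reader might infer that no outcome has a direction. Statistical Power implies one for lightness, and a hypothesis of no difference can be read as an ordinary null that is compatible with a directional alternative. This weakens any charge of outright contradiction. It does not justify the single tail, and it does not supply a direction for the other outcomes.
- **Arrest.** A reader might infer that arrest will be tested one-tailed towards KI benefit, so that harm could never be found. The outcome is categorical, a t test is not its natural analysis, and the article specifies no one-tailed test for it.
- **The effectiveness wording.** A reader might infer that the single tail makes this claim untestable, or that the article commits to reading non-significance as preserved effect. Neither is supported. The obstacle is that no margin or interval is set, and two-sided testing alone would not remove it. The phrase is aspirational and not a decision rule. Nor does the article say that KI weakens arrest; its Discussion says only that KI may reduce the free silver ions that cause staining.
- **Practical effect.** If the planned effect on lightness is real, power is above 99.9% with 27 to 30 per group under either tail, so the choice would hardly alter that result. This stands. It is equally a reason why nothing is gained by keeping the single tail.

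**Conclusion.** The point holds in a limited form. Data Analysis fixes a one-tailed t test at .05 with no justification and leaves the tail of its alternative open, while the hypothesis and the abstract give no direction. This doubles the false-positive allowance in the favoured direction from 2.5% to 5%, and it matters most for outcomes with no stated direction and for true effects smaller than the one planned. The critical values assume 27 completers per group; the power figures assume d = 1.594.

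The second part is separate and does not depend on the tail. The difference tests named cannot establish that effectiveness is uncompromised. The half-widths of 17 to 26 points (24 teeth per group) and 14 to 22 points (34 teeth per group) rest on assumed arrest of 70% to 90% and on independent teeth.

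**What to change.** 1. In Data Analysis, state that all comparisons, by t test or Mann-Whitney test, are two-sided at .05, and align the abstract and Statistical Power with this.
2. For caries arrest, report the SDF+KI minus SDF difference with a two-sided 95% confidence interval, and state that a non-significant difference will not be read as preserved effectiveness. Soften the wording in the Conclusions and the abstract to match. Whether to go further and set a non-inferiority margin is a matter for debate; the interval is useful either way.

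The cost is a few sentences, written before the data are analysed. No extra children or visits are needed.
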